## **Background**

There are currently no observational or randomized studies aimed at determining the optimal strategy for surveillance and outbreak prevention in the homeless shelter setting despite a history of well documented outbreaks with various pathogens including tuberculosis and respiratory viruses (1,2). Determining an optimal strategy is important in order to prevent outbreaks in high risk settings especially in the context of a viral pandemic such as the current SARS-CoV-2 pandemic. Outbreak prevention will decrease the mortality and morbidity associated with viral respiratory. This will naturally be associated with decreased healthcare related costs. Furthermore, surveillance for respiratory viruses, especially in the context of a pandemic, may empower a generally marginalized population.

## **Study Design**

We are conducting a prospective random cluster-allocation study to compare the effectiveness of four different surveillance regimens across eight shelters in Hamilton (four men’s and four women’s shelters). The shelters are associated with Good Shepherd, Mission Services, Wesley Urban Ministries, YWCA and Hamilton Native Women’s Centre; all have agreed to work with us on this study. The surveillance methods are as follows:

1. Active daily surveillance of symptoms and testing only symptomatic participants. This is the current standard of care protocol for residents accessing the shelters.
2. Once weekly self-collected oral swabs (OS) regardless of symptoms using written and visual instructions (attached).
3. Once weekly self-collected oral-nares swab (O-NS) regardless of symptoms using written instructions (attached).
4. Once weekly nurse collected nasopharyngeal swab (NPS) regardless of symptoms

[figure not shown]

All participants in the intervention groups will continue to receive active daily surveillance of symptoms. Only participants who provide consent will be considered in the intervention groups and verbal consent will be recorded by study staff at each site. At all sites participants who seek care for respiratory symptoms or symptoms potentially related to COVID-19 would get testing as is routinely done.

Each surveillance regimen will occur for 6-8 weeks based on the funding available. Each shelter has approximately 100 participants and we are aiming to enroll 30-50% of participants at each site.

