## **Outcomes**

1. Primary outcome: COVID-19 detection rate, i.e. the number of new positive cases over the study period in each arm of the study.
2. Secondary outcomes: Qualitative assessment of study enrollment over time. Percentage of participants who performed 50% or more of the weekly swabs in the intervention arms.

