## **Sample size considerations**

Since we are including our total sample frame, a sample size estimation at the cluster level is not required. However, if we succeed to enroll 50 participants per shelter from 8 shelters (n=400), and the detection rate is 3 times higher in the intervention groups (0.15) than in the comparator groups (0.05), we will have 90% power to detect a statistically significant and clinically important difference at a type I error rate of alpha=0.05 (one tailed), assuming an intraclass correlation of ~0.008. These computations were done using WinPEPI, and informed by conservative estimates from other studies on respiratory illness in the homeless (4, 5).

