## **Inclusion Criteria:**

1. Willing and able to provide verbal consent to participation in the study.
2. Male or female > 18 years of age, residing in one of the homeless shelters within Hamilton, ON.

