## **Exclusion Criteria:**

1. Unable or unwilling to give consent.
2. Male or female < 18 years of age.

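### The protocol does not settle who is counted in the control arm: consent is tied to the intervention groups in one section and required of everyone in others

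*Protocol*

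**What the plan says.** **Consent.** Protocol, Study Design, states the condition for one side of the comparison only: "Only participants who provide consent will be considered in the intervention groups and verbal consent will be recorded by study staff at each site". Of the control regimen, the same section says: "This is the current standard of care protocol for residents accessing the shelters". The eligibility sections make no distinction by arm. Inclusion Criteria asks for persons "Willing and able to provide verbal consent to participation in the study", and Exclusion Criteria rules out those "Unable or unwilling to give consent".

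**Enrolment.** Study Design: "Each shelter has approximately 100 participants and we are aiming to enroll 30-50% of participants at each site". Sample size considerations: "if we succeed to enroll 50 participants per shelter from 8 shelters (n=400". Neither statement exempts the control shelters.

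**Case finding and outcome.** Study Design: "At all sites participants who seek care for respiratory symptoms or symptoms potentially related to COVID-19 would get testing as is routinely done". Outcomes defines the primary outcome as "COVID-19 detection rate, i.e. the number of new positive cases over the study period in each arm of the study", with no denominator and no statement of whose positive results enter the count.

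**The concern.** Two features of Study Design leave the control-arm population open. First, the consent condition is attached to the intervention groups and nothing equivalent is said for the comparator. Second, the word participants is used there for everyone living in a shelter: about 100 per shelter, of whom a fraction is to be enrolled. A description of symptomatic testing of participants can therefore be read as covering every symptomatic resident of a control shelter.

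Routine testing continues at all sites, so positives will arise among people who never enrolled. If those in control shelters are counted while the swab arms count consenters only, the numerators come from source populations of different size and selection. Because the primary outcome is worded as a count, the difference in size alone moves the result. If denominators are added, the difference in selection remains. Allocating shelters at random does not protect against either.

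**Working it through.** **Inputs from the protocol**
- About 100 residents per shelter and 30-50% enrolled, i.e. 30 to 50 persons per shelter (Study Design).
- Detection 0.05 in the comparator and 0.15 in the intervention groups; n = 400; intraclass correlation about 0.008; one-sided alpha 0.05; stated power 90% (Sample size considerations).

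**Assumptions**
- Two shelters per arm (8 shelters / 4 regimens). The text does not state the split, and the design figure is not shown.
- The 0.05 applies equally to enrolled and non-enrolled control residents.

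**1. The plan's own figures.** 8 x 50 = 400, so the control shelters are planned at 50 enrolled each, the upper end of the 30-50% target.

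The design effect is 1 + (50 - 1) x 0.008 = 1.392. One-sided normal-approximation power after dividing n by 1.392 is:
- 200 vs 200, pooled variance: 0.884
- 100 vs 300, unpooled variance: 0.881
- 100 vs 300, pooled variance: 0.768

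The stated 90% is thus approximately reached under some standard variants; the protocol gives neither the split nor the variance form. For the present point, the power statement shows only that controls were planned as enrolled persons.

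**2. Expected cases per arm** = 2 x (persons counted per shelter) x (detection rate)

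| Persons counted | 30% enrolled | 50% enrolled |
|---|---|---|
| Swab arm, consenters | 60 x 0.15 = 9 | 100 x 0.15 = 15 |
| Control, consenters | 60 x 0.05 = 3 | 100 x 0.05 = 5 |
| Control, all residents | 200 x 0.05 = 10 | 200 x 0.05 = 10 |

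**3. Ratio of counts, swab arm to control**
- Consenters in both arms: 9/3 = 3.0 and 15/5 = 3.0.
- All residents in control: 9/10 = 0.9 and 15/10 = 1.5.

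The per-person detection ratio is 0.15/0.05 = 3.0 throughout; only the counting rule changes.

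**4. Adding denominators.** With all control residents counted, 9/60 or 15/100 = 0.15, against 10/200 = 0.05, a ratio of 3.0. The scale problem disappears, but the groups are then 30-50% volunteers on one side and all residents on the other.

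**5. All residents in every arm.** If enrolled residents of swab shelters are detected at 0.15 and the others at 0.05, shelter-wide detection is:
- 30% uptake: 0.3 x 0.15 + 0.7 x 0.05 = 0.08
- 50% uptake: 0.5 x 0.15 + 0.5 x 0.05 = 0.10

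Against 0.05 in control, the ratio is 1.6 to 2.0.

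**The case against.** The strongest reply is that the protocol, read as a whole, already requires consent in every arm. Both eligibility sections say so without exception, the enrolment target covers every site, and the sample size rests on 50 enrolled in each of eight shelters. The Study Design sentence is logically compatible with consent also being required of controls, and the standard-of-care sentence describes a regimen, not an analysis population. This stands, and it makes consenters in every arm the plainest reading.

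A reader might go further and infer that the plan does compare volunteers in the swab arms with all residents in the control arm. The documents do not support that: no section says that all control residents are counted, and the inference turns one sentence's silence into a rule against the eligibility and sample size sections.

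It can also be said that the 0.9 to 1.5 ratio depends on comparing raw counts, whereas the outcome is called a rate and the power statement uses proportions. That is correct for the size of the distortion, and on the proportion scale the ratio stays at 3.0. It does not settle whose positives count, and the outcome as defined is still a number of cases.

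The absence of a statement that consent precedes allocation is a silence, not an error, and the documents give no figure for how volunteers' risk differs from that of other residents. No size can be put on that selection from the text.

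Nor can the matter simply be left to an analysis plan. Whether control residents are approached and consented is a field procedure that cannot be supplied afterwards.

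**Conclusion.** The point holds as an internal inconsistency about who is counted in the control arm. It is not a demonstration that the arms are counted from different populations. Study Design states the consent condition for the intervention groups alone; the eligibility criteria, enrolment target and sample size imply it for all; and the primary outcome leaves open whether positives in non-enrolled control residents count.

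The choice matters: on the protocol's own rates, the primary count ratio is 3.0 under one reading and 0.9 to 1.5 under the other. These figures rest on two shelters per arm, equal uptake across arms within the 30-50% target, and a common 0.05 rate among enrolled and non-enrolled control residents.

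**What to change.** 1. **Study Design.** Reword the consent sentence to cover all four arms: residents of control shelters are approached, consented and enrolled by the same procedure as residents of the swab shelters, and only enrolled persons are counted in any arm. Keep the word participants for enrolled persons and use residents for everyone in a shelter.
2. **Outcomes.** Define the primary outcome as new positives among enrolled participants divided by the number enrolled, in every arm.
3. **Secondary sensitivity analysis.** Analyse de-identified confirmed cases among all residents over shelter census, from the same source for all eight shelters. Uniform consent alone does not remove self-selection if residents decide after their shelter's regimen is known; this analysis does not depend on consent.

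**Cost.** Items 1 and 2 are wording changes. Consenting 60 to 100 control residents (2 x 30 to 2 x 50) is already implied by the enrolment target and n = 400. Item 3 needs aggregate case counts and census figures that the protocol does not mention, including cases among people who did not consent. Its contrast is diluted to a ratio of about 1.6 to 2.0, so it should support the primary analysis and not replace it.

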## **Outcomes**

1. Primary outcome: COVID-19 detection rate, i.e. the number of new positive cases over the study period in each arm of the study.
2. Secondary outcomes: Qualitative assessment of study enrollment over time. Percentage of participants who performed 50% or more of the weekly swabs in the intervention arms.

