## **Data Collection Methods**

1. COVID-19 swab results will be processed as per usual protocol by the Virology Research Lab at St. Joseph’s Healthcare (SJH)

Specimens identified as positive in the research lab will be directed to the Clinical Virology Lab within HRLMP for confirmatory testing.

1. All swabs were placed into a viral inactivation medium and transported to the laboratory for COVID-19 testing. Briefly, total nucleic acid was extracted from specimens and then amplified by RT-PCR for the UTR and Envelope genes of SARS-CoV-2 and the human RNase P gene, which is used as a sample adequacy marker.

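### The primary outcome is called a detection rate but defined as a raw case count per arm, whereas the trial is powered on proportions of enrolled participants

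*Protocol*

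**What the plan says.** Under Outcomes, the protocol gives the primary outcome as "COVID-19 detection rate, i.e. the number of new positive cases over the study period in each arm of the study". No number of participants, swabs or person-weeks appears in the definition.

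Sample size considerations uses the same term differently. The calculation holds "if we succeed to enroll 50 participants per shelter from 8 shelters (n=400", and the assumed effect is that "the detection rate is 3 times higher in the intervention groups (0.15) than in the comparator groups (0.05". These values can only be proportions of the people enrolled.

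Three statements in Study Design bear on the missing denominator:

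- On enrolment: "Each shelter has approximately 100 participants and we are aiming to enroll 30-50% of participants at each site".
- On duration: "Each surveillance regimen will occur for 6-8 weeks based on the funding available".
- On who is counted: "Only participants who provide consent will be considered in the intervention groups". This sentence does not mention the standard-care arm, whereas the Inclusion Criteria require consent from every participant.

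Data Collection Methods adds that "Specimens identified as positive in the research lab will be directed to the Clinical Virology Lab within HRLMP for confirmatory testing". The outcome definition does not say whether a positive case means a confirmed one.

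**The concern.** The abbreviation that introduces the definition makes it operative: the detection rate is the number of cases. Taken literally, the arms are compared on a quantity that grows with the number of people who consented, even when the regimens find infection equally well.

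Consent is not assured to be equal across arms. The regimens range from symptom checks alone to a weekly nurse-collected nasopharyngeal swab, and the protocol makes enrolment over time a secondary outcome.

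This is not detail that can be left to a statistical analysis plan. The protocol states a primary outcome, and that outcome disagrees with its own power calculation. An analysis plan that added a denominator would be departing from the written definition.

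**Working it through.** **Inputs from the protocol.** 8 shelters and 4 regimens; about 100 residents per shelter; 30% to 50% enrolled; n = 400 (50 per shelter); detection 0.15 against 0.05; one-tailed alpha 0.05; intraclass correlation about 0.008; stated power 90%.

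**Assumption.** Two shelters per arm. The text does not give the allocation. A figure in Study Design that I could not see may show it.

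**Step 1: what quantity is the trial powered on?**

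Design effect = 1 + (50 − 1) × 0.008 = 1.392. Normal-approximation power for two proportions, with each group size divided by 1.392:

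| Split of participants | Pooled variance | Unpooled variance |
|---|---|---|
| 200 v 200 | 0.884 | 0.889 |
| 300 v 100 | 0.768 | 0.881 |

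The first row in full, pooled: effective n per group = 200/1.392 = 143.7. The null standard error is √(0.10 × 0.90 × 2/143.7) = 0.0354. The alternative standard error is √((0.05 × 0.95 + 0.15 × 0.85)/143.7) = 0.0349. Power = Φ((0.10 − 1.645 × 0.0354)/0.0349) = 0.884.

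The stated 90% is reproduced to within 2 points by three of the four entries. The protocol does not say which split was used. All of them require enrolled participants as the denominator; none can be computed from counts alone.

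**Step 2: what does the count do when enrolment differs?**

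Participants per arm: 2 × 30 = 60 at the bottom of the range, 2 × 50 = 100 at the top. Expected count = participants × true detection proportion.

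| True detection | Count, 60 enrolled | Count, 100 enrolled | Ratio of counts | Ratio of proportions |
|---|---|---|---|---|
| 0.05 in both arms | 3 | 5 | 1.67 | 1 |
| 0.15 in both arms | 9 | 15 | 1.67 | 1 |

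A true 3-fold effect is distorted in the same way:

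- 0.15 in the smaller arm and 0.05 in the larger: 9 v 5 cases, a ratio of 1.8.
- 0.15 in the larger arm and 0.05 in the smaller: 15 v 3 cases, a ratio of 5.

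**Step 3: consequence for a test (illustration that ignores clustering).**

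Both arms have the same true risk, with 60 and 100 participants. A one-sided 5% conditional binomial test asks whether the larger arm detects more. Results are from 200,000 simulated trials per row.

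| True risk in both arms | Rejects on raw counts (null share 1/2) | Rejects with denominators (null share 100/160) |
|---|---|---|
| 0.05 | 8.1% | 1.5% |
| 0.10 | 17.7% | 2.0% |
| 0.15 | 25.5% | 2.0% |

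The excess over 5% in the middle column comes only from the missing denominator.

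**The case against.** **The intended denominator can be guessed.** The sample-size section points to enrolled participants, and a careful analyst would probably divide by them. That lowers the likelihood of harm. It does not remove the contradiction, because the written definition says something else.

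**The 1.67 is an extreme.** It needs both shelters of one arm at the floor of the enrolment range and both of another at the ceiling. This stands: it is an upper limit within the planned range, not an expectation.

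**A count might be meant as yield.** Study Design sets out to "compare the effectiveness of four different surveillance regimens across eight shelters in Hamilton", and the shelters are of similar size. Cases per shelter would then approximate yield per resident, with uptake as part of what makes a regimen effective. This is a coherent target, but the protocol does not state it and the power calculation does not use it. One part of the objection survives. If consent follows allocation (the order is not stated), a denominator of consenters is fixed after allocation, and uptake should remain visible.

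**Three stronger readings are tempting, and the documents do not support them.**

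- *Arms followed for different lengths.* A reader might infer that one arm runs 6 weeks and another 8, so that 60 × 6 = 360 and 100 × 8 = 800 participant-weeks differ 2.2-fold. But the duration depends on funding, and the outcome refers to a single study period. One common length, not yet known, is the more natural reading.
- *Unconfirmed positives inflating the weekly-swab arms.* With an assumed per-test specificity of 99% to 99.9%, 6 to 8 completed swabs would add 0.6 (1 − 0.999⁶) to 7.7 (1 − 0.99⁸) percentage points per uninfected participant. The specificity is not in the protocol, research-lab positives are already sent for confirmation, and nothing says that unconfirmed results count. What is left is a wording gap.
- *All residents counted in the standard-care arm, only consenters elsewhere.* The consent sentence could be read that way, but the Inclusion Criteria ask consent of everyone. The population rule needs stating; an unequal one is not established.

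**Conclusion.** The point holds in a limited form. The primary outcome as defined is a raw count per arm and does not match the proportion on which the trial is powered. Within the protocol's own enrolment range, equal detection could appear as a count ratio of up to 1.67, against a planned ratio of 3. The size rests on two shelters per arm and on opposite ends of the enrolment range falling in different arms; with equal enrolment and a common duration the distortion vanishes. The false-rejection figures are illustrative and ignore clustering. The mismatch between definition and power basis rests on no assumption. It should be corrected because it concerns the primary outcome and the correction is cheap.

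**What to change.** Redefine the primary outcome as the proportion of enrolled participants with at least one confirmed SARS-CoV-2 positive over the study period, each participant counted once. Apply the same consented-population rule in all four arms. This matches the 0.15 and 0.05 under Sample size considerations.

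In addition:

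- Report the rate per participant-week as a supporting analysis.
- State that the duration within 6-8 weeks, whatever funding allows, is the same in every arm.
- Report the number enrolled in each arm beside the primary result, because consent may follow allocation and uptake would otherwise be hidden by the denominator.

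**Cost.** A short change of wording and no extra testing. Enrolment must be recorded in every arm, including standard care, with dates. The supporting rate also needs departure dates, which take some effort to collect among shelter residents. The new denominator does not remove selection through consent; reporting enrolment by arm only makes it visible.

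### No infection history is taken at entry, so already diagnosed residents who still test positive can be counted as new cases, almost only in the swab arms

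*Protocol*

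**What the plan says.** The Outcomes section gives the primary outcome as a detection rate, namely "the number of new positive cases over the study period" in each arm. It does not say whether *new* means acquired after entry, first positive within the study, or first positive ever.

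On eligibility, the first inclusion criterion reads "Willing and able to provide verbal consent to participation in the study" and the second adds age and residence in a Hamilton shelter. The exclusions are "Unable or unwilling to give consent" and age under 18. The protocol describes no entry test and no question about earlier infection.

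Testing differs by arm (Study Design). The comparator is "Active daily surveillance of symptoms and testing only symptomatic participants", which is also the existing standard of care in these shelters. The other three arms add a weekly swab for everyone, for example "Once weekly nurse collected nasopharyngeal swab (NPS) regardless of symptoms". Symptomatic people are tested at all sites. Each regimen runs for 6-8 weeks, depending on funding.

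Under Data Collection Methods, specimens are "amplified by RT-PCR for the UTR and Envelope genes of SARS-CoV-2", and "Specimens identified as positive in the research lab will be directed to the Clinical Virology Lab within HRLMP for confirmatory testing". The second test rechecks positivity. It does not date the infection.

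**The concern.** An endpoint that counts new cases needs some means of telling a new case from an old one, and the protocol provides none. If RNA stays detectable after illness, someone diagnosed shortly before enrolment can give a positive study swab. In a swab arm that person is tested in the first week without needing symptoms. In the comparator the same person, now recovered, is not tested. The error therefore runs in one direction and falls on the primary comparison.

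A second, milder issue concerns people who are infected but undiagnosed at entry. The first swab finds those accumulated before the study, while later swabs find roughly one week's new infections each. The total therefore combines a first-round prevalence yield with a continuing weekly yield, and the mix changes with a duration that is not yet fixed. This affects how the result is interpreted. It is not in itself a bias in a detection rate.

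**Working it through.** **The plan's own figures.** Sample size considerations assumes detection of 0.15 against 0.05, a ratio of 3, with 50 people in each of 8 shelters, an intraclass correlation of 0.008, one-sided alpha of 0.05 and 90% power. The design effect is 1 + 49 × 0.008 = 1.392. With the pooled-variance formula, four shelters against four (200/1.392 ≈ 144 effective per side) gives power of 0.884. Two comparator shelters against six swab shelters gives 0.881 with unpooled variance and 0.768 with pooled variance. The stated 90% is thus approximately reproduced under some variants. The present point does not depend on it.

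**Scale against the planned effect.** Assume two shelters per regimen (the split is not stated), hence 6 × 50 = 300 people in the swab arms. Suppose a proportion q of them are already diagnosed, still positive and counted as new within the planned 0.15. Without them the ratio is (0.15 − q)/0.05:

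- q = 1% (3 people): 0.14/0.05 = 2.8
- q = 2% (6 people): 2.6
- q = 3% (9 people): 2.4
- q = 5% (15 people): 2.0

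The documents do not give q, so this range is an assumption. Each three such people account for 0.01/0.05 = 0.2 of the ratio.

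**Illustration of the mechanism.** All inputs except the number of weeks are assumptions: constant weekly incidence i; perfect swab sensitivity; positivity lasting D = 2-4 weeks; half of infections found by symptoms, before the study as well as during it; all known cases still resident and enrolled. With k weekly swabs over k weeks:

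- Swab arm, everyone counted: D·i at the first swab plus (k − 1)·i later.
- Already diagnosed at entry: 0.5·D·i.
- Swab arm without them: 0.5·D·i + (k − 1)·i.
- Comparator: 0.5·k·i.

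| k | D | Ratio, everyone counted | Ratio, known cases removed | Known cases as share of swab-arm count | First-swab share after removal |
|---|---|---|---|---|---|
| 6 | 2 | 7/3 = 2.33 | 6/3 = 2.00 | 1/7 = 14% | 1/6 = 17% |
| 6 | 3 | 8/3 = 2.67 | 6.5/3 = 2.17 | 1.5/8 = 19% | 1.5/6.5 = 23% |
| 6 | 4 | 9/3 = 3.00 | 7/3 = 2.33 | 2/9 = 22% | 2/7 = 29% |
| 8 | 2 | 9/4 = 2.25 | 8/4 = 2.00 | 1/9 = 11% | 1/8 = 12.5% |
| 8 | 3 | 10/4 = 2.50 | 8.5/4 = 2.13 | 1.5/10 = 15% | 1.5/8.5 = 18% |
| 8 | 4 | 11/4 = 2.75 | 9/4 = 2.25 | 2/11 = 18% | 2/9 = 22% |

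If only a fraction f of the known cases are still resident and enrol, the k = 6, D = 3 ratio is (6.5 + 1.5f)/3. It runs from 2.17 at f = 0 to 2.67 at f = 1. The last column shows how the legitimate first-round share falls as the study lengthens from 6 to 8 weeks.

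**The case against.** The strongest reply is that this is a detection endpoint in a comparison of surveillance regimens. Finding an undiagnosed, asymptomatic resident at the first swab is what testing regardless of symptoms is for. That stands.

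A reader might infer that every infection present at entry inflates the swab arms, and set 2.67 against 5i/2.5i = 2.0, the ratio when counting starts after the first round in both arms. The documents do not support that reading. It treats a detection rate as an incidence rate, and it discards true detections along with the old cases. Nor are infections present at entry invisible in the comparator: those that later cause symptoms are tested there.

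A reader might also note that entry positivity of 1-10% added to a common rate of 0.05 gives ratios of 0.06/0.05 = 1.2 to 0.15/0.05 = 3.0 with no real difference. That supposes equal detection of new infection in all arms, whereas the swab arms receive weekly swabs on top of daily symptom surveillance. It is not a false-positive rate for this trial.

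A further reply is that *new*, in its ordinary sense, already leaves out a person with a known earlier positive, and that the detailed rule may sit in an analysis plan that is not shown. The first half is fair: nowhere does the protocol say that such people are counted. The second half helps only in part. An analysis plan can define *new*, but it cannot reliably apply the definition if infection history was never recorded, and recording it is a matter for the protocol.

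Finally, first swabs may be spread over the study if enrolment is staggered, so the first-round yield need not fall in one calendar week. That is why the fix works by each participant's own swab number.

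**Conclusion.** The point holds in a limited form. The protocol builds its primary outcome on new cases, collects nothing that identifies an old one, and tests people without symptoms only in the swab arms. Already diagnosed people who remain positive can therefore enter the count almost only there, which favours swabbing. Undiagnosed infections found at the first swab belong in the detection rate, but they should be visible as a first-round yield because their share depends on the 6-8 week duration.

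The size is unknown, since the documents give neither entry prevalence nor duration of positivity. On the stated assumptions, removing known cases moves the ratio from 2.67 to 2.17 at D = 3 and 6 swabs. Over D = 2-4 the change is from 2.33-3.00 to 2.00-2.33 with 6 swabs, and from 2.25-2.75 to 2.00-2.25 with 8. These changes are upper-end, because they assume that every known case is still resident and enrols. The problem should be corrected, but it does not make the trial uninterpretable.

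**What to change.** 1. At consent, in all four arms, ask about previous laboratory-confirmed COVID-19 and its date.
2. In Outcomes, define a new case as a participant's first positive in the study, counted once, excluding from the count anyone with a known recent positive before entry. State in advance what counts as recent. This concerns counting only and changes neither who is tested nor how anyone is managed.
3. Keep the total detection rate, so defined, as the primary outcome.
4. Report positives on a participant's first swab separately from later ones. Add a supportive comparison that starts counting after each participant's first study week, in the comparator as well. It should not rank equally with the total, because it leaves out genuine detections.

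The cost is one consent question, one extra table, and fewer events in the supportive comparison. No extra tests are needed. Self-reported history will miss some earlier diagnoses, so the correction will be incomplete, but without the question it cannot be made reliably.
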